### 2.5. Ethical Considerations

The focus groups will be audio- and video-recorded. The individual face-to-face interviews will only be audio-recorded. The transfer of voice and image rights in the case of focus groups and of voice rights only in the case of individual interviews will be requested. In the context of COVID-19 (data collection for this study coincided with the COVID-19 pandemic during times of significant restrictions in Catalonia, Spain, such that the measures explained in this section had to be taken to continue implementing the project. These changes were accepted by the Research Ethics Committee.), we might audio- and video-record virtual interviews using Microsoft Teams. Participants must give their informed written consent. Participants under the age of 16 must also present the consent of their parent or legal guardian. This is known as double consent. Participants aged 16 to 18 are considered to be mature minors and will not need the consent of their parent or legal guardian. In the quantitative study, the questionnaires are anonymous and voluntary. Participants under the age of 16 must provide an informed consent form signed by them and their parent or legal guardian.

This protocol follows the tenets of the Declaration of Helsinki [37]. The research protocol was approved by the Research Ethics Committee (REC) of the Institut d’Investigació en Atenció Primària Jordi Gol (IDIAP). Approval dates were: February 2017 (Ethics reference number: P17/048) for the qualitative part of the study; July 2020 (Ethics reference number: 19/074-P) for the whole mixed-methods project. It also has the approval of the Management of ASSIR Catalunya and the editorial committee of the WSJ. All the directors of the education centres where the study will be conducted will be adequately informed.

Due to COVID-19, Microsoft Forms and Microsoft Teams software might be used. In this case, we will guarantee data protection, in accordance with the Regulation (EU) 2016/679 of the European Parliament and Council of April 27 on Data Protection (RGPD) and the Spanish Organic Law 3/2018 of December 5, on the Protection of Personal Data and guarantee of digital rights. The online questionnaire can only be answered by people aged 16 and over since the necessary consent cannot be obtained from children under 16. Consequently, the first question in the online questionnaire is if they agree to answer it, and the second if they are 16 or older. Responses from those under 16 will be collected using the paper questionnaire at the education centres and ASSIR units.

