### 2.3. Sample/Participants

Participants will be teenagers and young adults aged 14 to 25 able to express themselves in one of the two official languages of Catalonia (Catalan or Spanish). We will exclude people who do not wish to participate in the investigation and people under 16 who wish to participate but whose parents/legal guardians do not sign the informed consent form. 

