#### 2.3.2. Quantitative Part of the Study

We have devised three methods for participant recruitment: (1) convenience sampling will be used in education centres (high schools, vocational training schools, training and insertion programs and universities); (2) consecutive sampling will be used to recruit young people who consult the ASSIR units; (3) young people who access the WSJ of their own accord will be invited to participate. These three methods will be used to invite participants to join the study; participation will be voluntary. Recruitment is more fully developed in the data collection Section 2.4.2.

Based on the size of the effect of the differences in the assessment of the WSJ contents, and depending on whether they consulted the website of their own accord or not, a total sample of 776 participants will be required, accepting an alpha risk of 0.05 and a beta risk of 0.2 in a two-sided test. Up to 388 subjects will be necessary in the first group and 388 in the second to find a statistically significant proportion difference, expected to be of 0.5 in group 1 and 0.4 in group 2.

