#### 2.4.2. Quantitative Part of the Study

In the context of COVID-19, we have both an online (Microsoft Forms) and paper version of the questionnaire (Teleform). The online questionnaire can be accessed via direct link or QR code. The questionnaire consists of 24 closed questions and 2 open-ended questions. The questionaire is available in Supplementary Material (Figure S1).

At the education centres: The recruiting researchers will communicate with these centres to disseminate the questionnaire among students. The centre directors will decide if their centre will use the online or paper questionnaire.At the ASSIR units: a wide network of professionals are also researchers that will recruit for the study. The study will be disseminated through posters in the waiting rooms and at the counter of each ASSIR unit. These posters will contain the study instructions and the QR code for the questionnaire so that young people can quickly download it to their mobile phone and answer it. There will also be a paper version of the questionnaire for people unable to access it digitally. Digital users of the ASSIR will be sent the link to the questionnaire with information to encourage them to answer on the same platform they used for the consultation (email, WhatsApp^®^, e-consultation).WSJ users who make email inquiries will automatically receive an email with the direct link to the questionnaire, encouraging them to participate after explaining that this is a study to evaluate the website. The study will be also advertised on the WSJ homepage through images with a direct link to the questionnaire.

Whatever the origin of the participant, the variables that will be evaluated for all the participants in the sample through the questionaire are the following:

Sociodemographic variables: age, sex, gender identity, sexual orientation, country/culture of origin, years of residence in Spain, postal code, socioeconomic condition of the postal code according to the Territorial Socio-Economic Index, city/rural/semirural residence, current job, ongoing studies, type of access to the questionnaire (electronic or paper).

Variables related to the WSJ: prior knowledge of the WSJ, use of the WSJ, usability of the WSJ, usefulness of the WSJ, rating of affective-sexual education content.

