Variables related to social media: ability to access to digital resources, use of other webpages of affective-sexual education, following affective-sexual education influencers, use of pornography webpages.

Variables related to study recruitment: Participants from educational centers and ASSIR units will access the survey by indication of the professionals. The third contacting group will access it by themselves, without anyone’s indication. The sample calculation has been performed based on this variable.

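### The own-accord group can hold only ages 16–25 while the professional-indicated group spans 14–25, and the comparison the study is sized for sets no common age range

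*Protocol article*

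**What the plan says.** All references are to the protocol article.

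- **Eligibility (2.3).** "Participants will be teenagers and young adults aged 14 to 25".
- **Sample size (2.3.2).** The comparison is between those who consulted the website of their own accord and those who did not, "accepting an alpha risk of 0.05 and a beta risk of 0.2 in a two-sided test". Proportions are "expected to be of 0.5 in group 1 and 0.4 in group 2", and "Up to 388 subjects will be necessary in the first group and 388 in the second".
- **How the groups are formed (2.4.2).** Respondents from education centres and ASSIR units count as directed by a professional. Those who come through the website count as own accord. Of this recruitment variable the article says "The sample calculation has been performed based on this variable".
- **Questionnaire mode by route (2.4.2).** Website users who write in by email get a link, and "The study will be also advertised on the WSJ homepage through images with a direct link to the questionnaire". No paper form is described for this route. ASSIR units have both forms. At education centres, "The centre directors will decide if their centre will use the online or paper questionnaire".
- **Age bar (2.5).** "The online questionnaire can only be answered by people aged 16 and over since the necessary consent cannot be obtained from children under 16". The same section says that under-16s answer on paper at the education centres and ASSIR units.
- **Analysis (2.6.2).** Chi-squared or Fisher tests relate the website assessment to the sociodemographic variables. A regression follows if an association is found. No age range is set for the route comparison.
- **Objectives (1.2.4).** Age and motivation for consulting the website are both listed as factors that may go with different ratings.

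**The concern.** The recruitment and consent rules together give the two compared groups different age ranges. At 14–15 there are indicated respondents and no own-accord respondents, so no data exist on the route contrast at those ages. If 14–15-year-olds rate the website differently from older respondents, part of that age difference shows up as a difference between own-accord and indicated users. It can create an apparent effect of motivation or hide a real one.

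This affects the one comparison that determines the sample size, and the imbalance is fixed by the design before any data are collected. The limitations section mentions the burden of double consent but not this consequence.

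**Working it through.** **1. Age range by group, from the stated rules**

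| Group | Route | Mode | Ages possible |
|---|---|---|---|
| Own accord | Website (email link, homepage link) | Online only | 16–25 |
| Indicated | Education centres | Online or paper | 14–25 (under 16 on paper) |
| Indicated | ASSIR units | Online or paper | 14–25 (under 16 on paper) |

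The ranges overlap at 16–25 only.

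**2. The plan's own sample size**

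Inputs from 2.3.2: 0.5 versus 0.4, two-sided alpha 0.05, beta 0.2. With pooled variance under the null and no continuity correction:

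n = [1.960·√(2·0.45·0.55) + 0.842·√(0.5·0.5 + 0.4·0.6)]² / 0.10² = (1.379 + 0.589)² / 0.01 = 387.3, rounded up to 388 per group and 776 in total.

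The stated figure reproduces, and power at 388 per group is 0.80. The issue is comparability and not arithmetic.

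**3. Unadjusted false-positive rate with no true route effect**

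The article does not give the next three inputs, so they are assumptions:
- f, the share of 14–15-year-olds in the indicated group: 10–30%;
- d, how much lower the 14–15-year-olds' favourable proportion is: 0.10 or 0.20;
- a proportion of 0.45 at ages 16 and over in both groups (the midpoint of the plan's two values).

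Then p₁ = 0.45 and p₂ = 0.45 − f·d, so the spurious gap is f·d. With 388 per group, the rejection rate is Φ((f·d − 1.96·SE₀)/SE₁) plus the negligible opposite tail, where SE₀ is the pooled and SE₁ the unpooled standard error.

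Example, f = 0.3 and d = 0.20: p₂ = 0.39, gap 0.06, SE₀ = √(2·0.42·0.58/388) = 0.0354. The gap is 1.69 standard errors and the rejection rate is 0.395.

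| Share f | d = 0.10: gap, rejection | d = 0.20: gap, rejection |
|---|---|---|
| 10% | 0.01, 5.9% | 0.02, 8.7% |
| 20% | 0.02, 8.7% | 0.04, 20.3% |
| 30% | 0.03, 13.4% | 0.06, 39.5% |

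If f = 0 or d = 0, the rate is the nominal 5%. A base proportion of 0.50 gives almost the same figures (38.8% in the last cell).

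**4. Would the conditional adjustment be triggered?**

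Suppose age is split at 16 and tested against the rating in all 776 respondents. At f = 0.2 there are 78 aged 14–15 and 698 older. For d = 0.10 (0.35 versus 0.45), SE₀ = 0.0593 and SE₁ = 0.0572, so power = Φ((0.10 − 1.96·0.0593)/0.0572) = 0.39. For d = 0.20 the same formula gives about 0.94. Over f = 10%, 20% and 30%, power is about 0.22, 0.39 and 0.52 for d = 0.10, and 0.71, 0.94 and 0.99 for d = 0.20.

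**5. Power after restriction to 16–25**

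With 388 own-accord and 388·(1 − f) indicated respondents, 0.5 versus 0.4:

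| Share f | Indicated aged 16+ | Power |
|---|---|---|
| 0 | 388 | 0.80 |
| 10% | 349 | 0.78 |
| 20% | 310 | 0.75 |
| 30% | 272 | 0.72 |

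**The case against.** **Regression can deal with it.** A reader might infer that no model can repair the comparison. That goes too far. With 14–15 entered as its own age level, those respondents carry no information on the route coefficient, and confounding from that age band is removed for ages 16–25. What cannot be estimated is the route effect at 14–15. Age is recorded for everyone, so the repair is available. However, Section 2.6.2 does not commit to it.

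**The adjustment would be triggered when it matters.** This is largely right for a 20-point age gap once the share reaches 20% (step 4), so the largest rates in step 3 would seldom go unadjusted if the triggered model included age suitably coded. It is weaker for a 10-point gap, where the trigger fires about 22–52% of the time, though the bias is then also small.

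**The size rests on assumed inputs.** This stands. No share or age gap is given, 14–15 covers two of twelve eligible years, and the limitations section expects double consent to hinder under-16 participation. The lower rows of the table may be nearer the truth.

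**The study is descriptive and the age bar is a consent constraint.** Both are true, and the age bar itself is not criticised. A descriptive contrast still needs a stated age range if the reader is to know what is being compared.

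**Centres that go online lose their under-16s.** A reader might infer this from the directors' choice of mode. The article does not say it: Section 2.5 provides paper for under-16s at the centres. The two statements can be read together, with online for those aged 16 and over and paper for the rest, but Section 2.4.2 presents a choice for the whole centre without that exception.

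**Conclusion.** The concern holds in a limited form. The stated rules make it certain that the two groups have different age ranges with no overlap at 14–15, and nothing in the article confines the comparison to the ages they share.

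It would be too strong to call the comparison confounded as a matter of fact. Confounding also needs ratings to differ by age, which Section 1.2.4 poses as a question to be answered. The false-positive rates in step 3 apply to the unadjusted test under the assumed share and age gap. The sample size is correct for its stated inputs, and the problem can be remedied with data already being collected.

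**What to change.** 1. In Section 2.6.2, restrict the own-accord versus professional-indicated comparison to ages 16–25, and adjust for age within that range whatever the bivariate result.
2. Report 14–15-year-olds separately, described as professional-recruited, paper-only respondents.
3. State in Section 2.3.2 that under-16s do not count toward this comparison, and give the resulting power for a plausible range of shares (step 5).
4. Reconcile Section 2.4.2 (directors choose the mode for the centre) with Section 2.5 (under-16s answer on paper at the centres), so that the procedure for under-16s at a centre using the online form is explicit.

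The cost is a change of wording and the power loss in step 5 if 388 indicated participants are recruited in all. No new data item is needed. Keeping 388 aged 16 or over in the indicated group would mean recruiting 388/(1 − f), that is 432, 485 or 555 at a 10%, 20% or 30% share. That is a larger commitment and is not part of this recommendation.

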### 2.6. Data Analysis

#### 2.6.1. Qualitative Part of the Study

A discourse analysis (Why do they say this?) of participants in the focus groups and individual interviews will be conducted [38,39]. We selected discourse analysis because we aim to understand the hegemonic discourses and counter-discourses constructed by young people about the affective-sexual education they receive [40]. For this analysis, we will use ATLAS- ti (version 8).

#### 2.6.2. Quantitative Part of the Study

We will perform a descriptive analysis of all variables, using frequencies and percentages for categorical variables and mean and standard deviation for age and years living in Spain. Familiarity with the website will be summarized with a percentage and confidence interval. The bivariant analysis will be performed using Pearson’s chi-squared test or Fisher’s exact test to find associations between the assessment of WSJ and the sociodemographic variables. If the bivariant analysis shows any associations, a multivariant analysis using a regression model with assessment of WSJ as the outcome variable is planned. The anlaysis will be performed disaggregating by gender. Significance level is set at 5%. SPSS statistical package for Windows, version 25.0, will be used for all analyses.

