#### 1.2.4. Quantitative Part of the Study

General objective: To understand how the youth population of Catalonia evaluates the WSJ.

Specific objectives:To determine what content of the WSJ receives the best rating by young people.To identify whether assessment of content and usability of the WSJ varies according to the following factors: age, sex, gender identity, sexual orientation, culture of origin, socioeconomic status, area of residence (urban, semiurban or rural) and motivation for consulting the website (of their own accord or suggested by a professional).To identify whether assessment of content of the WSJ is different in young people that had previously used it.To assess if having previously consulted the ASSIR unit is associated with a different assessment of the WSJ content.To determine if the target population knows about the WSJ, and what percentage use it and consider it useful.To evaluate if socioeconomic conditions determine the use of paper vs. digital questionnaires.To determine if young people in Catalonia visit other affective-sex education websites, and which are the most popular.To determine if young people in Catalonia follow any influencers for affective-sexual education, and which influencers are the most popular.To determine the percentage of young people in Catalonia that visit pornography websites.

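### Familiarity and use of the website are to be summarised for the target population from a sample partly recruited through that website, with no separation by recruitment route

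*Protocol article*

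**What the plan says.** The aim, among the specific quantitative objectives in section 1.2.4, is "To determine if the target population knows about the WSJ, and what percentage use it and consider it useful".

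Section 2.3.2 names three recruitment routes. In the first, "convenience sampling will be used in education centres". The second is consecutive sampling of young people who consult ASSIR units. In the third, "young people who access the WSJ of their own accord will be invited to participate". Section 2.4.2 explains how the third route works: people who email the site receive the questionnaire link automatically, and "The study will be also advertised on the WSJ homepage through images with a direct link to the questionnaire". The same section collects prior knowledge and use of the WSJ from every participant, whichever route brought them in.

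The end of section 2.4.2 contrasts the two routes in which a professional points the participant to the survey with the website route, and says the sample size was calculated on this contrast. Section 2.3.2 sets that size at 388 per group, 776 in total.

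For the analysis, section 2.6.2 states that "Familiarity with the website will be summarized with a percentage and confidence interval". Use falls under the general rule of "using frequencies and percentages for categorical variables". The only breakdown stated is "disaggregating by gender". The Limitations section does not mention recruitment route.

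**The concern.** The quantity of interest is the share of 14- to 25-year-olds who know and use the site. For one route, selection depends on that quantity: to be invited, a person must be on the homepage or have written to the site's email service. If this route is combined with the others, the resulting percentage depends on how many people were recruited through the site as well as on how well known the site is.

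The abstract links the evaluation of familiarity and use to improving the site and adapting the resources allocated to it. An inflated percentage with a tight confidence interval would overstate the site's reach to the people making those decisions. The interval reflects sampling error only and gives no warning of this error.

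**Working it through.** **Inputs from the article.** Proportions 0.5 and 0.4, two-sided alpha 0.05, beta 0.2, 388 per group and 776 in total (section 2.3.2). The grouping is website route against the two professional-indicated routes (end of section 2.4.2).

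**Inputs assumed.** The article gives no familiarity rate. Let p be familiarity among website recruits, q familiarity among the other participants, and w the website share of the sample.

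**The plan's own figure.** With pooled variance, n per group = [1.96 × √(2 × 0.45 × 0.55) + 0.8416 × √(0.5 × 0.5 + 0.4 × 0.6)]² / 0.1² = (1.379 + 0.589)² / 0.01 ≈ 387.3, rounded up to 388. The stated sample size is reproduced, and there is no fault in it. It implies w = 388/776 = 0.50.

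**Pooled percentage.** P = w × p + (1 − w) × q. The excess over the other participants is P − q = w × (p − q). The nominal 95% half-width is 1.96 × √(P(1 − P)/776).

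| w | p | q | P | Excess (points) | Half-width (points) |
|---|---|---|---|---|---|
| 0.50 | 1.00 | 0.10 | 0.55 | 45 | 3.5 |
| 0.50 | 1.00 | 0.30 | 0.65 | 35 | 3.4 |
| 0.50 | 1.00 | 0.50 | 0.75 | 25 | 3.0 |
| 0.50 | 0.80 | 0.10 | 0.45 | 35 | 3.5 |
| 0.50 | 0.80 | 0.20 | 0.50 | 30 | 3.5 |
| 0.50 | 0.80 | 0.40 | 0.60 | 20 | 3.4 |
| 0.25 | 1.00 | 0.20 | 0.40 | 20 | 3.4 |

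In every row the excess is several times the half-width, so the interval excludes q.

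**Where the effect shrinks.** With w = 0.50, p = 1.00 and q = 0.80 the excess is 0.50 × 0.20 = 10 points. With p = q = 0.80 it is zero. The problem is therefore largest when the site is little known outside its own visitors.

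**Without the website route.** For the 388 participants from the other two routes together, the half-width is 1.96 × √(q(1 − q)/388): 3.0 points at q = 0.10, 4.0 at 0.20, 4.9 at 0.40 and 5.0 at 0.50.

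**The case against.** The strongest reply is that section 2.6.2 names no denominator and never says the three routes are combined. Route is a recorded variable, so a breakdown could be produced, and a condensed article may leave analysis populations to a fuller document. This stands in part: pooling is a reading of the text. But the article does fix the summary, the interval and one breakdown, and it collects these variables from everyone regardless of origin. Followed as written, that yields a pooled figure, at odds with the article's own population aim.

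A reader might also infer more than the article supports:

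- **That half the sample is a website quota.** The 388 is what the comparison of 0.5 with 0.4 requires. No cap or allocation per route is set, and the achieved website share may be smaller or larger.
- **That every website recruit knows and uses the site by definition.** The variable is prior knowledge, and a first-time homepage visitor may have none. Values of p below 100% are plausible, which is why a range is shown.
- **That the same inflation affects every population percentage.** Another objective is "To determine the percentage of young people in Catalonia that visit pornography websites", and others concern other websites and influencers. For these, nothing in the article establishes a direction or size of bias from the website route, and a confidence interval is promised for familiarity only.
- **That the education-centre arm would give the true population value.** It is a convenience sample confined to education and training settings. Standardising it by age and sex would not change that, and the article does not state its size.

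Familiarity and use belong to one of nine specific quantitative objectives. The sample size and the planned tests concern assessment of the site and are not affected by this point.

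**Conclusion.** The point holds for familiarity and use. The article sets a population aim, recruits one comparison group through the site itself, and plans a summary that does not separate that group. The pooled percentage is inflated by w × (p − q) whenever website recruits know the site more often than the rest.

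The size cannot be fixed from the article. Over the assumptions tabulated, the excess is 20 to 45 points against a nominal half-width of 3.0 to 3.5 points. It would be smaller if the site is already widely known, if many website recruits are first-time visitors, or if the website share is low.

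The excess is measured against the other participants, who are not themselves a random sample of young people in Catalonia. Removing the website route takes out this avoidable error but does not make the remaining figure a population estimate.

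**What to change.** In section 2.6.2:

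- Report familiarity and use by recruitment route: education centres, ASSIR units and website.
- Exclude the website route from any statement about familiarity or use in the target population, and do not headline a pooled figure.
- State that the education-centre and ASSIR figures come from a convenience and a consecutive sample, and that ASSIR attenders may know the site more often, so neither is a population estimate.
- Report perceived usefulness by route as well, but keep the website users, who are well placed to judge it.

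No new data are needed, because route is already a study variable. The cost is precision: about ±3 to ±5 points for the two non-website routes together at n = 388. Each route taken alone would have a wider interval, by an amount that depends on a split the article does not give.

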#### 1.2.2. Specific Objectives of the Project

To outline a new participatory model of affective-sexual education for adolescents and young adults led by midwives and/or nurses that incorporates the gender perspective and sexual and socioeconomic diversity (we will use the Territorial Socio-Economic Index (IST) to determine socioeconomic conditions. This is a synthetic index that summarizes in a single value several socioeconomic characteristics of the population by small areas. The index includes data on employment, educational level, immigration and income of all people living in each territorial unit, based on six sectoral indicators [31]) and that can be used by health professionals working with young people.To provide a new framework for the WSJ that is competitive and effective with regard to the affective-sexual education of young people.To involve the target population in the creation of this intervention for their emotional and sexual wellbeing.

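### The bivariate step tests numeric age with chi-squared or Fisher only, which ignores its order and, if the effect is a gradient, loses power

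*Protocol article*

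**What the plan says.** Section 2.6.2 describes categorical variables by frequencies and percentages, and reports the "mean and standard deviation for age and years living in Spain". For associations it names Pearson's chi-squared or Fisher's "exact test to find associations between the assessment of WSJ and the sociodemographic variables". No trend, rank, t-type or correlation test appears at this step. Section 2.4.2 places age, years of residence in Spain and the "socioeconomic condition of the postal code according to the Territorial Socio-Economic Index" among the sociodemographic variables, so all three fall under that sentence.

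The next sentence of 2.6.2 is conditional. "If the bivariant analysis shows any associations", then "a multivariant analysis using a regression model with assessment of WSJ as the outcome variable is planned".

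The second specific objective in 1.2.4 asks whether the assessment of content and usability "varies according to the following factors: age, sex, gender identity, sexual orientation, culture of origin, socioeconomic status" and further factors. Age and socioeconomic status are in that list; years in Spain is not. Section 1.2.2 says that the socioeconomic index "summarizes in a single value several socioeconomic characteristics of the population by small areas", but no section says whether it is analysed as a number or in bands.

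**The concern.** A contingency-table test needs categories. If age is held as a number, it must be grouped or each year must become its own category. No cut-points are given for the questionnaire data, so the result would depend on a later choice. Either way the test treats the categories as unordered: a steady rise in rating from 14 to 25 counts no more than the same differences in scrambled order. If the true pattern is a gradient, this costs power on a factor that the study set out to examine.

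The bivariate result also decides whether the regression is fitted, so a weak test at this step can affect what is examined later.

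**Working it through.** **The plan's own figure.** Section 2.3.2 gives 388 per group for 0.5 versus 0.4, two-sided alpha 0.05, beta 0.2. With the pooled-variance formula and p̄ = 0.45:

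n = [1.960·√(2·0.45·0.55) + 0.842·√(0.25 + 0.24)]² / 0.1² = 1.968² / 0.01 = 387.3, rounded up to 388, or 776 in total.

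This reproduces exactly. It concerns a binary comparison (access on a professional's indication versus of one's own accord, section 2.4.2), for which chi-squared is suitable. The present point does not touch it.

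**Inputs for the age check.** From the protocol: age range 14 to 25, two-sided 5% level. Assumed, because the protocol does not say: ages uniform over the 12 single years; a linear effect of age; an effect size at which a 1-df numeric test has 80% power.

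**Step 1. Noncentrality.** 80% power on 1 df at the 5% level needs λ = 7.85.

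**Step 2. Information kept by grouping.** The variance of uniform ages 14 to 25 is (12² − 1)/12 = 11.917, with mean 19.5. For 14–18 (5 years, mean 16) versus 19–25 (7 years, mean 22), the between-group variance is (5/12)·3.5² + (7/12)·2.5² = 8.75. The share kept is 8.75/11.917 = 0.734. This split is illustrative only: section 2.3.1 uses it for qualitative sampling, and nothing applies it to the questionnaire.

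**Step 3. Power.** Multiply λ by the share kept and read the power from the noncentral chi-squared distribution on (groups − 1) df.

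| Coding of age | Share kept | λ | df | Power |
|---|---|---|---|---|
| Numeric, linear | 1 | 7.85 | 1 | 80% |
| 14–18 vs 19–25 | 0.734 | 5.76 | 1 | 67% |
| 14–19 vs 20–25 | 0.755 | 5.93 | 1 | 68% |
| 3 equal groups | 0.895 | 7.03 | 2 | 66% |
| 4 equal groups | 0.944 | 7.41 | 3 | 62% |
| 12 single years | 1.000 | 7.85 | 11 | 41% |

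Finer grouping keeps more information but spreads it over more degrees of freedom, so power still falls.

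**Step 4. Cross-check.** A calculation with N = 776, a binary assessment with 45% positive (assumed) and a linear logit effect set to give 80% power (odds ratio about 1.23 per SD of age) gives 67%, 68%, 66%, 62% and 41% for the same five categorical codings. With N = 388 the power figures are the same to the nearest point, with a larger odds ratio (about 1.34), because the effect is recalibrated to 80%.

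**The case against.** The strongest case against has five parts.

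- **A regression is planned.** A reader might infer that chi-squared and Fisher are the only association analyses. They are not: the regression can take age as a number, and nothing requires it to be grouped there. This stands, and it limits the point to the bivariate step.
- **The condition is loose.** A reader might infer that a missed age gradient means no adjusted model. The text asks for any association, so one other positive factor may be enough to trigger the regression. However, the text does not say whether age would then enter the model. The loss is possible, not certain.
- **The index and years in Spain.** A reader might infer that three numeric factors of interest are affected. The protocol does not support that. The index is absent from the list of variables given a mean and SD, and it may be held in bands. Years in Spain is numeric but belongs to no stated objective. Only age is both shown to be numeric and named in an objective. If the index is banded, the bands would still be ordered, so a trend test remains relevant.
- **Linearity is assumed.** If ratings rise and then fall with age, an unordered test can detect what a linear test misses. This stands, and the fix allows for it.
- **An article condenses.** Cut-points and covariate form are commonly left to a fuller document, and their absence is no fault. Here, though, the article states a test and assigns it to the whole class of sociodemographic variables, including two that it treats as numeric. The point is about that stated choice.

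**Conclusion.** The point holds for the bivariate step, as a minor and inexpensive improvement. As written, 2.6.2 applies unordered categorical tests to age, which the same paragraph treats as numeric and 1.2.4 names as a factor of interest. For a linear effect that a numeric test would detect with 80% power, and uniform ages, the loss is about 12 to 18 points with two to four groups (power 68% to 62%) and 39 points with single years (80% to 41%). These figures depend on the assumed age distribution, effect shape and grouping, none of which the protocol gives. They illustrate the cost and do not predict the study's power for age, since the sample size was not based on age.

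Describing age by its mean and testing it in groups is inefficient rather than contradictory, and no stated figure is wrong.

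**What to change.** In 2.6.2:

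1. Keep chi-squared and Fisher for unordered factors such as sex, gender identity, sexual orientation and culture of origin.
2. For age and years in Spain, test the association by regressing the assessment on the numeric value (logistic if the assessment is binary, ordinal if graded), and enter age as a numeric term in the multivariable model.
3. For the socioeconomic index, state the form in which it is held. Use the numeric value if it is a number, or a linear-by-linear trend test if it is in ordered bands.
4. Because a linear term can miss a non-monotone pattern, add a quadratic term for age or show the grouped table alongside.

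The cost is a few lines of analysis text. It needs no new data, no further participants and no change to the sample size, and the methods are standard in the named software.
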